### Phase 3: Scale-Up and Sustainability (October 2025-June 2027)

In the final phase, the intervention will be scaled up to cover health care facilities across all 10 districts. This gradual expansion is planned over a period of 3 years, allowing for iterative refinement of the approach, capacity building of providers, and sustained engagement with stakeholders at each stage of implementation. The study population includes 300 MH providers and managers (nurses, midwives, auxiliary nurse midwives, doctors, and community health workers [ASHAs]) in selected private and public facilities across 10 districts in Assam with diverse geographic settings, as well as state-level managers or policymakers. We also anticipate reaching 225,000 pregnant/postnatal women through the chatbot.

### Data Management and Analysis

#### Overview

The data collection with postnatal women, providers, facility assessments, and service use statistics will be completed by trained research assistants using tablet computers. Upon completion of any electronic data collection form, all data will be immediately encrypted. Encrypted data cannot be decrypted without the unique private encryption key, to which only study investigators will have access. Encrypted survey data will be stored on research tablets until it can be transmitted to password-protected, study-specific servers using the local cellular data network. If cellular data service is unavailable at a given facility, the data collection team leader’s laptop computer will function as a central synchronization and backup point until the team reaches an area where mobile data service is available.

#### Qualitative Analysis

Qualitative data from the IDIs will be transcribed verbatim, translated into English where appropriate, and typed in Word. The data will be analyzed using Nvivo15 (Version 15; Lumivero) [25]. The analysis will entail open coding and progressive categorization of issues based on inductive (examining relevant issues that emerge from the data) and deductive approaches (examining key issues identified at the design stage). Themes will be further modified as more issues emerge from the data analysis. Categories derived from the data will be further refined through analysis charts. Hard copies of study documents will be stored under lock and key in secure drawers/rooms at PCC in New Delhi. We will upload digital recordings and store them on password-protected computers in folders on a secure network. We will store all data for at least 3 years before being destroyed by PCC.

#### Quantitative Analysis

Raw quantitative data collected from the postnatal women’s survey (dipstick survey) will be cleaned and checked for errors and outliers. Data cleaning and quality checks will occur fortnightly during collection with a comprehensive pass before midline and endline analyses. Descriptive statistics (means, SDs, medians, and frequencies) will summarize baseline characteristics and outcomes. The primary outcome, the composite quality score of maternal and newborn care [24] and secondary outcomes (service uptake indicators, user-reported knowledge and self-care practices, and satisfaction with care) will be compared between baseline and follow-up.

Normality will be tested (Shapiro-Wilk). Parametric (*t* tests, ANOVA) or nonparametric (Wilcoxon and Mann-Whitney) tests will be used as appropriate. Categorical variables will be analyzed using chi-square or Fisher exact test. Multivariable analyses will use generalized linear/logistic mixed models to adjust for clustering (facility/district) and confounders (age, parity, socioeconomic status, dose of exposure-engagement frequency, and enrollment channel). For repeated measures, mixed-effects models will assess changes over time. Multiple comparisons will be adjusted using Bonferroni or FDR. All analyses will be performed in IBM SPSS Statistics (Version 29.0; IBM Corp) and R Core Team. Results will be visualized with tables and graphs. Statistical significance is set at *P*<.05, with effect sizes and 95% CIs reported.

Interim analyses will be conducted after midline data (Phase 2) collection completion in 2026; final analyses will be performed after endline data collection in 2027.

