#### Monitoring and Iterative Improvement

The monitoring and evaluation process will be conducted on users and health care providers. This study uses a mixed method, pre-post implementation design to evaluate the introduction and scale-up of the e-SAATHI MH chatbot in Assam. While this design enables comprehensive assessment of both quantitative outcomes and qualitative experiences, we acknowledge that the absence of randomization limits the strength of causal inference. To address potential sources of bias, we will implement several strategies, including adjustment for district-level clustering, accounting for secular trends over time, and controlling for measured confounders in the analysis. These approaches aim to strengthen the validity of our findings and provide a nuanced understanding of the intervention’s impact in real-world settings.

All the developed data collection instruments and procedures will be pretested in settings like those in which they will be administered. Guidance will be sought from postnatal women who have recently given birth when finalizing the instruments to ensure that questions and the data collection procedures are conducted with appropriate sensitivity and are not perceived as stigmatizing. The study tools will be pretested among a small group of women with characteristics similar to those of the study population to identify potential negative consequences and will be modified accordingly. Study tools for postnatal women will be translated and pretested in Assamese and Hindi.

The study comprises 5 main data collection tools that are described in Table 1: (1) in-depth qualitative interviews with MH providers; (2) in-depth qualitative interviews with postnatal women; (3) telephone interviews with postnatal women and MH chatbot users; (4) health facility inventory; and (5) MH digital platform program data.

**Table 1. T1:** Data collection activities.^a^

	1. IDIs^b^ with health care providers	2. IDIs with postnatal (PN^c^) women	3. Survey with PN women	4. Facility inventory and routine data	5. MH^d^ data from chatbot platform
Study population	Purposively selected providers from various care levels (public and private)	Purposively sampled PN women using chatbot <6 mo since childbirth	PN women recently given birth in last 2‐8 wk	Facility providing MH services	Pregnant and PN women onboarded to chatbot (deidentified)

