The study uses a mixed methods approach to comprehensively document and monitor the rollout of the mental health chatbot for pregnant and postnatal women in Assam. Implementation is guided by continuous field feedback, data on onboarding and user engagement with the chatbot, the effectiveness of online campaigns, and qualitative and quantitative impact assessments. By adopting a participatory CLA methodology, the program integrates women’s perspectives and feedback from the earliest proof of concept, beginning in 5 facilities and then expanding across 3 districts to ultimately reach 10 districts within 3 years. These iterative CLA cycles, paired with regular evaluations of operational and financial sustainability, foster a deeper understanding of implementation challenges, including acceptability and feasibility. Upon completion of phase 2, a detailed impact evaluation will assess the effectiveness of the intervention, ensuring that crucial insights and real-world evidence are retained throughout the study’s progression. User engagement with the chatbot will be tracked as an automatically generated metric, supporting ongoing learning and adaptation to enhance the system. For the qualitative interviews and dipstick surveys, which are single, one-time interactions, with no follow-up assessments. However, we will systematically record and report the number of individuals who refuse participation or cannot be contacted at recruitment, along with reasons for refusal when volunteered. For the chatbot, we will also report the number of users who disengage before completing the interaction.

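### Unclustered tests picked by a normality test stand beside clustered mixed models for the baseline/follow-up comparison, and the plan does not say which gives the primary inference

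*Protocol article*

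**What the plan says.** In the protocol article, Quantitative Analysis states that the composite quality score (primary) and the secondary outcomes "will be compared between baseline and follow-up". It goes straight on to test selection: "Normality will be tested (Shapiro-Wilk"), after which t tests or ANOVA, or "nonparametric (Wilcoxon and Mann-Whitney) tests will be used as appropriate". Categorical outcomes get chi-square or Fisher exact tests.

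The next sentence adds: "Multivariable analyses will use generalized linear/logistic mixed models to adjust for clustering (facility/district) and confounders". A further sentence reads: "For repeated measures, mixed-effects models will assess changes over time". Nothing ranks these analyses or says which one carries the conclusion on the primary outcome.

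Monitoring and Iterative Improvement bears on this in three places:

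- It commits to "adjustment for district-level clustering" as one answer to the lack of randomization.
- It has survey women approached in the postnatal ward of a facility and builds the score as a sum of binary items, often rescaled to a percentage.
- It describes the "dipstick surveys, which are single, one-time interactions, with no follow-up assessments".

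**The concern.** Women who deliver in the same facility share its staff, supplies and practice, and the primary outcome is a score of the care received. Their scores will therefore be correlated. The t, ANOVA, Wilcoxon, Mann-Whitney, chi-square and Fisher procedures take no account of that. The mixed models do. With both planned and neither designated, each outcome can end with two P values that disagree, and the choice between them stays open until the data have been seen.

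Two features add to this. Letting a normality test choose the procedure means that the quantity tested depends on the data: a rank test does not estimate the change in score, which is how the Results section defines the primary outcome. The list also includes methods that need repeated measurements on the same unit, which the survey does not supply for women.

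**Working it through.** **Inputs.** The article gives no power calculation, standard deviation, intraclass correlation (ICC) or number of surveyed facilities, so there is no stated figure to reproduce.

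- From the article: significance at 0.05 (Quantitative Analysis; two-sided assumed) and 200 postnatal women (Table 1; whether per wave or in total is not stated, and 200 per wave is assumed).
- Assumed: m = 10 or 20 women per facility, that is 200/10 = 20 or 200/20 = 10 facilities per wave; ICC 0.05 or 0.10; and a between-wave correlation of facility effects (CAC) of 0.5 to 1.0 where the same facilities are surveyed twice.

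**Step 1: different facilities in each wave.** The variance of the wave difference is inflated by DEFF = 1 + (m − 1) × ICC. The true type I error of an unclustered test is 2 × [1 − Φ(1.96/√DEFF)].

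| m | ICC | DEFF | Effective n per wave | Type I error |
|---|---|---|---|---|
| 10 | 0.05 | 1 + 9 × 0.05 = 1.45 | 200/1.45 = 138 | 10.4% |
| 10 | 0.10 | 1 + 9 × 0.10 = 1.90 | 200/1.90 = 105 | 15.5% |
| 20 | 0.05 | 1 + 19 × 0.05 = 1.95 | 200/1.95 = 103 | 16.0% |
| 20 | 0.10 | 1 + 19 × 0.10 = 2.90 | 200/2.90 = 69 | 25.0% |

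Simulation of the t test under the same four settings gave 10.4%, 15.6%, 16.4% and 25.6%. With 40 facilities (m = 5) the formula gives 7.4% at ICC 0.05 and 9.8% at ICC 0.10.

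**Step 2: same facilities in both waves.** Part of the facility effect cancels, and the factor becomes 1 + (m − 1) × ICC − m × ICC × CAC.

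- Lowest error: m = 10 or 20, ICC 0.10, CAC 1.0. For m = 20 this is 1 + 1.9 − 2.0 = 0.90, a type I error of 3.9%, slightly conservative.
- Intermediate: m = 20, ICC 0.10, CAC 0.8. This is 1 + 1.9 − 1.6 = 1.30, or 8.6%.
- Highest error: m = 20, ICC 0.10, CAC 0.5. This is 1 + 1.9 − 1.0 = 1.90, or 15.5%.

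So the direction of the error depends on facility overlap between waves, which the article does not state. It does describe roll-out from 5 facilities to 3 and then 10 districts (Population), so a changing set of facilities is plausible.

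**Step 3: the normality test.** The item count is not given. In simulations of summed yes/no items at n = 200, Shapiro-Wilk rejected in all or nearly all samples for scores of 10 to 25 items when women share one success probability. It rejected less often for longer scores or when women vary: 77% with 25 items and 56% with 40 items under a Beta(6,4) spread between women. Across settings the range was about 56% to 100%. If 200 is the total over three waves (200/3 ≈ 67 per wave), the range widens to roughly 15% to 100%. Rejection is therefore frequent but not certain.

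**Step 4: pairing.** Each survey woman is interviewed once, 2 to 8 weeks after delivery, so baseline and follow-up hold different women. A signed-rank test, a paired t test or a woman-level repeated-measures model would have no linked survey records to use.

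**The case against.** The strongest reply is that the plan already handles clustering. The same paragraph specifies mixed models for facility and district, and the design section repeats a clustering commitment. That stands: a reader might infer that the plan ignores clustering or that the primary test has wrong standard errors, but the article supports neither, because it designates no primary test. What remains is that the unclustered tests come directly after the statement of the primary comparison and nothing subordinates them to the models.

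A reader might also infer that the listed tests assume pairing. Mann-Whitney and the independent t test do not, the t tests are never called paired, and Wilcoxon could mean the rank-sum version. Reading it as signed-rank rests only on its listing beside Mann-Whitney. Likewise the repeated-measures sentence need not concern survey women: quarterly facility inventories and monthly client counts are truly repeated. The conflict with the one-time surveys is conditional, although the paragraph opens with the dipstick survey.

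Nor can it be said that Shapiro-Wilk will always reject; Step 3 shows otherwise. The section also promises effect sizes and 95% CIs, so a mean difference could still be reported beside a rank test.

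Finally, every ICC, facility count and overlap figure here is assumed. Up to 300 facilities are planned, and spreading 200 women more thinly would shrink the inflation. Degrees-of-freedom methods and the exact random-effects structure properly belong to an SAP. The coexistence of two incompatible analyses is in the published text, however, and is not an omission of detail.

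**Conclusion.** The point holds as a failure to rank analyses that can give conflicting answers. If the unclustered tests were used for inference, a nominal 5% test would have a true type I error of about 10% to 26% with different facilities in each wave, and about 4% to 15% with the same facilities, depending on between-wave correlation. These figures rest on 200 women per wave, 10 to 20 facilities and ICC 0.05 to 0.10, none of which the article fixes. If the mixed model carries the inference, this inflation does not arise. The normality screen adds a substantial chance that the primary outcome is tested by a method that does not estimate its stated quantity. The pairing problem applies only if a signed-rank test, a paired t test or a woman-level repeated-measures model is actually used on survey data. The point should be settled before the 2026 interim analysis.

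**What to change.** State in Quantitative Analysis that the primary analysis of the percentage score is the facility-clustered mixed model already planned, with survey wave as a fixed effect, reporting the mean difference and 95% CI. Use the logistic version for binary secondary outcomes. Then:

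- keep the t, ANOVA, rank, chi-square and Fisher results as descriptive only;
- drop the Shapiro-Wilk step for the survey outcomes;
- limit paired and repeated-measures methods to data that are in fact repeated, such as facility records.

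The degrees-of-freedom method and the exact random-effects structure can be left to the SAP.

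The cost is a few sentences of wording. No new data are needed, and the named software (SPSS and R) fits these models. Confidence intervals may be wider than those from the simple tests, most of all if facilities change between waves.

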### Chatbot

A key component of the e-SAATHI project is the chatbot messaging on MH information. It consists of a set of weekly tips and periodic reminders/check-ins that we send to subscribed users from prenatal week 10 through postnatal week 15. Women can subscribe to the free program in 1 of 2 ways: (1) clicking on a social media advertisement; or (2) scanning a QR code while visiting a health facility (public or private) that has engaged with the project. Both actions launch an automated conversation in WhatsApp that prompts the woman to onboard to the askNivi chatbot (accept terms and conditions and provide basic demographic information) and then subscribe to the ANC/PNC program (initially provide expected due date and preferred provider). Women who scan a QR code at a facility have the option of getting 1-on-1 support from a provider—typically a nurse—trained in user onboarding. The messages will be developed in alignment with the National Health Mission and WHO, ANC, and PNC guidelines (Figure 1).

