## Results

The e-SAATHI study was formally funded in September 2022, marking the commencement of project activities. Since the initiation of the program, significant progress has been achieved in both the onboarding of health care facilities and participant recruitment. As of December 2025, a total of 210 health facilities across Assam have been successfully integrated into the e-SAATHI network. A total of 201,813 women have been enrolled to receive MH support through the chatbot platform.

Chatbot-based data collection was launched in April 2023 and is scheduled to continue through June 2027, ensuring comprehensive coverage of the intervention period. The collection of qualitative and quantitative evaluation data began in November 2023, providing a robust foundation for assessing both user experiences and measurable outcomes.

Interim analyses are planned following the completion of midline data collection in 2026, which will offer early insights into the effectiveness and operational feasibility of the intervention. Final analyses are scheduled to take place after endline data collection in 2027, at which point the full impact of the e-SAATHI program will be evaluated and published. The primary outcome of interest is the change in the composite quality score of maternal and newborn care, serving as a key indicator of the intervention’s effectiveness. Secondary outcomes include a range of service uptake indicators, user-reported knowledge and self-care practices, and satisfaction with care received. The study will also assess operational feasibility, including the integration of providers into the digital system and the identification of barriers such as digital literacy and connectivity challenges.

As of the writing of this paper (December 2025), we are completing phase 2 and initiating in-depth impact evaluation.

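### Engagement frequency and enrollment channel are listed as confounders of a baseline versus follow-up comparison, although both arise only after a woman joins the chatbot

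*Protocol article*

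**What the plan says.** The Quantitative Analysis section deals with the survey of postnatal women. The composite quality score and the secondary outcomes "will be compared between baseline and follow-up". The Results section agrees: "The primary outcome of interest is the change in the composite quality score of maternal and newborn care".

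The multivariable sentence in Quantitative Analysis then has generalized linear or logistic mixed models adjust for facility/district clustering and for "confounders (age, parity, socioeconomic status, dose of exposure-engagement frequency, and enrollment channel".

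The Monitoring and Iterative Improvement section states the design: "This study uses a mixed method, pre-post implementation design to evaluate the introduction and scale-up of the e-SAATHI MH chatbot in Assam". Among the measures against bias it names "accounting for secular trends over time, and controlling for measured confounders in the analysis".

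The Chatbot section shows where channel comes from. "Women can subscribe to the free program in 1 of 2 ways", namely "1) clicking on a social media advertisement; or (2) scanning a QR code while visiting a health facility". A woman who never subscribes has no channel. The article describes no separate dose-response or users-only model.

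**The concern.** A confounder of a before-and-after contrast has to be settled before the exposure acts. Age, parity and socioeconomic status meet that test. Engagement frequency does not, because it is the amount of chatbot a woman received. Channel does not either, because it comes into being when she subscribes.

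Holding both fixed asks how the score changed between waves for women with the same chatbot use, in effect none. The study wants to know how much the score changed because the chatbot was introduced.

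Two errors could follow. A benefit delivered through women's own use may be adjusted away. Conversely, a trend that would have occurred anyway stays in the coefficient and may be read as the programme effect. The second matters because the article itself names secular trends as a threat to this uncontrolled design.

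**Working it through.** The article gives no effect size, SD or power for this comparison, so there is no stated figure to reproduce.

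**Step 1: what the period coefficient means.** Let T = 0 at baseline and 1 at follow-up, D = engagement frequency, S = joined by advertisement, Q = joined by QR code. With the listed covariates the linear part is

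E[Y] = b0 + b1·T + b2·D + b3·S + b4·Q + (age, parity, socioeconomic status).

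Setting D = S = Q = 0 shows that b1 is the change at zero chatbot use. Equivalently, b1 = total change − the part predicted by dose and channel.

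**Step 2: when it cannot be estimated.** If no baseline woman is a user and every follow-up woman is, each follow-up woman has exactly one channel, so S + Q = T. The columns 1, T, D, S, Q are then linearly dependent and b1 has no unique value. This is algebra and needs no assumed effect size. It does need channel coded as none / advertisement / QR code.

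The article does not settle whether these conditions hold:
- The Population section says chatbot users take part in the surveys. The third data collection tool, under Monitoring and Iterative Improvement, also admits women who may not have used the chatbot.
- The Results section dates chatbot data from April 2023 and evaluation data from November 2023, so an unexposed baseline is not established.

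**Step 3: size, under stated assumptions.** The simulation used ordinary least squares with 2,000 runs per scenario.
- From the article: 200 postnatal women (Table 1), read here as 200 per wave.
- Assumed: SD 15, mean engagement of about 10 units in users, 0.5 points per unit, channels split 50:50, no facility or district effects.

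The expected change through use is 0.5 × 10 × (user share at follow-up − user share at baseline). At 80% versus 0% users this is 0.5 × 10 × 0.8 = 4.0, so Step 1 predicts:
- no trend: b1 = 4.0 − 4.0 = 0
- 3-point trend: b1 = 7.0 − 4.0 = 3.0
- 2-point provider-side effect: b1 = 6.0 − 4.0 = 2.0

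Mean estimates of the period effect:

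| Users at baseline / follow-up | Added component | Period only | Period + dose + channel (SE) |
|---|---|---|---|
| 0% / 100% | none | 5.06 | not estimable in any run |
| 0% / 80% | none | 4.04 | 0.02 (2.62) |
| 0% / 50% | none | 2.50 | −0.02 (1.84) |
| 20% / 80% | none | 3.02 | −0.04 (1.88) |
| 20% / 100% | none | 4.06 | 0.11 (2.63) |
| 0% / 80% | trend, 3 points | 7.02 | 3.01 (2.61) |
| 0% / 50% | trend, 3 points | 5.46 | 2.93 (1.84) |
| 0% / 80% | provider-side, 2 points | 6.00 | 1.94 (2.61) |
| 0% / 50% | provider-side, 2 points | 4.53 | 2.04 (1.84) |

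In the 80% and 50% rows with an unexposed baseline and no added component, the adjusted test rejected in about 5% of runs, the nominal level.

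**Step 4: where the loss is only partial.** Suppose use brings a flat 5 points whatever the dose, and the model adjusts for dose but not channel. The adjusted estimates are then 5.01 (100% users), 2.18 (80%) and 0.78 (50%), against period-only values of 5.01, 4.00 and 2.49. With channel added, they are −0.03 (80%) and −0.05 (50%).

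If channel is coded only as one route versus everything else, the model with 100% users can be fitted. With the dose-proportional effect it gives 0.03 (SE 2.89) against 5.03.

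**The case against.** **The sentence names no exposure term.** Change over time has its own sentence, without a covariate list, and the article is a condensation, so dose and channel might be meant for an analysis among users. This has some force, because channel would be a reasonable covariate there. It does not rescue the text. Among users, dose would be the exposure studied, still not a confounder. The section opens with the survey and its baseline versus follow-up comparison, and the design section ties confounder control to the pre-post design. Survey contacts are also described as one-time, so the repeated-measures sentence does not clearly take that comparison over.

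**The unadjusted tests remain.** They do, and they are unaffected. They do not, however, deliver the control of confounding and clustering that the article promises.

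**Channel carries selection differences.** It may, among users. It is a route into the programme, so a reader who calls it the intervention itself goes too far.

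**Stronger readings are tempting.** A reader might infer that an effective chatbot must be reported as having no effect, or that the model cannot be fitted at all. The documents support neither. A coefficient near zero needs no trend and no provider-side effect, and with dose alone it also depends on the shape of the dose-response. Non-estimability needs the conditions in Step 2 of the working. Nor is confounder adjustment the only safeguard: clustering and secular trends are named as well, and limited causal inference is admitted.

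**Conclusion.** The point holds in a limited form. The covariate list puts two post-enrollment variables among the confounders of a baseline versus follow-up contrast. The adjusted period coefficient then describes change at zero chatbot use. It is missing some or all of the effect through women's own use, still contains any secular trend or provider-side effect, and under one configuration of the survey samples is not estimable.

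The meaning of the coefficient and the rank result follow from the model and need no numerical assumption. The size of the bias does: it depends on the user share at each wave, the dose-response shape, the SD and the coding of channel, none of which the article gives. The simulated figures are therefore illustrations of direction, not forecasts.

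**What to change.** Remove engagement frequency and enrollment channel from the confounder list of the baseline versus follow-up model. Adjust that model only for age, parity and socioeconomic status, with facility/district clustering and a time trend where it can be estimated.

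Report engagement and channel in a separate secondary analysis among chatbot users, labelled non-causal.

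Do not replace the period contrast with onboarded versus not onboarded women. That is a different estimand, and it brings in the user/non-user selection that the Limitations section acknowledges.

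The cost is a sentence or two in the analysis section and no new data collection. The change is best made before the interim analysis planned for 2026.
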